**Figure Fig1:**
[figure not shown]
**Fig. 1** A Brief Flowchart of the Study

In non-diabetic patients with suspected CAD, coronary angiography (CAG) will be performed with the standard technique. Percutaneous coronary intervention (PCI) will be performed in culprit lesions based on the decision of an interventionist in participating centers within Korea [14]. Non-culprit lesions (index lesions) with intermediate stenosis (percentage diameter stenosis, 30–60%) by CAG will be evaluated by VH-IVUS if the patients meet the study inclusion and exclusion criteria. Data will be stored for off-line analysis.

Patients will be randomized at ratio of 1:1 using a random table (made by matches of age, sex, presentation of coronary artery disease and sequentially numbered) to receive either rosuvastatin 10 mg plus fenofibrate 160 mg or rosuvastatin 10 mg alone. Study drugs will be administered after the index VH-IVUS. Biochemical laboratory tests (fasting state) will be performed at the time of CAG and followed up at the third month (±2 months) and 12th month (±2 months). Follow-up CAG and VH-IVUS examination will be performed at the 12th month (±2 months). Clinical events will be followed up by office visit or by telephone contact if necessary. Adherence to the study drugs will be checked at every outpatient visit, and the decision to discontinue any of the study drugs will be discussed and checked under the recommendation of the responsible cardiologist. Other drugs which influence lipid profiles will be prohibited during the trial period.

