### Study objectives and hypotheses

The primary objective of this study is to compare the changes in percentage necrotic core volume (NCV) and absolute NCV in non-culprit intermediate lesions in non-diabetic, combined dyslipidemia patients after 12 months’ therapy with statin plus fenofibrate compared to statin alone. The working hypothesis of this trial is that statin plus fenofibrate combination therapy is superior to statin alone therapy in reducing the 12-month percentage NCV and the absolute NCV. The secondary objective is to compare changes in percentage and absolute dense calcium (DC), fibrofatty (FF) and fibrous (F) plaques, the incidence of and changes in thin cap fibroatheroma (TCFA), the changes in variables of grey scale IVUS (volumes of external elastic membrane, lumen, and plaque), and the remodeling index between the statin plus fenofibrate and statin alone groups. In addition, secondary endpoints will include comparisons of major adverse cardiac events (MACEs) at 12 months, defined as all-cause death, CV death, nonfatal myocardial infarction (MI), stroke, and ischemia-driven revascularization of intervened and non-intervened lesions between the two groups. In order to identify the mechanisms of plaque stability and regression, the relationships between the variables of the VH-IVUS parameters and laboratory markers, including lipids, inflammatory markers, and metabolic markers, in the statin plus fenofibrate and statin alone groups will be investigated. The incidence of drug adverse effects will be another secondary endpoint of the study.

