### Study population and entry criteria

Inclusion criteria are as follows: (1) age ≥ 20 years; (2) presence of non-culprit intermediate lesions confirmed by index CAG; and (3) combined dyslipidemia (baseline LDLc ≥ 70 mg/dL and non-HDLc ≥ 130 mg/dL in statin-naïve patients, and baseline LDLc ≤ 100 mg/dL and non-HDLc ≥ 100 mg/dL in patients on statin treatment). A non-culprit lesion is defined as a VH-IVUS-feasible native coronary lesion with 30–60% stenosis, 2.0–4.0 mm in diameter by visual estimation during CAG, and located more than 10 mm apart from the intervened lesion.

Exclusion criteria are as follows: (1) diabetic patients; (2) poor cardiac, renal, or hepatic function; (3) explicit side effects and/or contraindications to lipid-lowering agents, including pregnancy, breastfeeding, and familial hypercholesterolemia; (4) very high triglyceridemia (TG ≥ 500 mg/dL); (5) lesions that might cause difficulties for VH-IVUS. Detailed inclusion and exclusion criteria are summarized in Table 1.

**Table 1 Tab1:** Inclusion and exclusion criteria

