**Fig. 2 Fig2:**
[figure not shown]
Schedule of enrolment, interventions, and assessments

Written informed consent for subjects who meet clinical and angiographic inclusion and exclusion criteria will be obtained by an investigator. Personal information is planned to be corrected by interview and chart review. All personal information will be protected by an encoding process. Potential participants are informed of the purpose of the study, the potential hazards and risks, the potential benefits, the procedure, and the expected follow-up after intervention. They are informed that participation is voluntary and that withdrawal from the study may occur at any time. On the consent form, participants will be asked if they agree to the use of their data should they choose to withdraw from the trial. Participants will also be asked for permission for the research team to share relevant data with people from the universities taking part in the research or from regulatory authorities, where relevant. This trial involves collecting biological specimens for storage. Additional permission for storage and measurement of biological specimens will be acquired from participants according to the local IRB’s requests.

After the subjects are enrolled in the present study, subjects will be randomized to two groups using a random box table made by stratified randomization according to subjects’ age, sex, and clinical presentation (acute coronary syndrome or not).

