#### Study endpoints

The primary endpoint of this study is the comparison of the change in percentage NCV and absolute NCV between statin plus fenofibrate and statin alone groups of non-diabetic, combined dyslipidemia patients with non-intervened intermediate coronary artery disease at 12 months. The secondary endpoints are as follows: 1) comparisons of the changes in other tissue components of percentage and absolute plaque volume in index non-intervened lesions, including DC, FF, and F; 2) change in plaque phenotypes such as TCFA; 3) change in grey IVUS parameters, including vessel area/volume, lumen area/volume, plaque area/volume, and remodeling index; 4) MACEs for 12 months, including all cause death, CV death, nonfatal myocardial infarction, stroke, and ischemia-driven revascularization of intervened and non-intervened lesions; 5) relationships between the changes in tissue components of plaque and changes in laboratory findings; 6) adverse reactions to the study drugs, including myalgia, elevation of CPK more than twice the upper limit of normal, and hepatic dysfunction (alanine aminotransferase more than three times the upper limit of normal).

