### Statistical analyses

The primary endpoint of percentage NCV and absolute NCV will be analyzed using a paired-sample *t*-test or Wilcoxon rank-sum test for changes within each group, and an unpaired *t*-test or Mann–Whitney U test for differences between the two groups. Continuous variables will be expressed as mean ± standard deviation and compared by either a Student’s *t*-test or Mann–Whitney U test based on whether or not the data are normally distributed. Categorical variables will be expressed as number or percentage and compared by χ^2^ or Fisher’s exact test. Pearson correlation test will be used to evaluate the correlation between the changes in percentage NCV and absolute NCV, and changes in laboratory findings from baseline to follow-up. These statistical analyses will be performed in the entire index non-culprit segment and the most severe 10-mm segment centered on the minimal lumen area.

Multivariable linear regression analysis will be performed in order to identify the independent predictors of the reduction in percentage NCV. To analyze the secondary endpoints, VH-IVUS parameters, grey IVUS parameters, and angiographic parameters will be analyzed using a paired sample *t*-test or Wilcoxon rank-sum test for changes within each group, and an unpaired *t*-test or Mann–Whitney U test for differences between the two groups. Correlations between these parameters and laboratory variables will be evaluated by the Pearson correlation test.

Changes in the phenotypes of the index lesions between the two groups will be compared by χ^2^ or Fisher’s exact test. The composite endpoint of CV events will be analyzed by comparing the Kaplan–Meier event rates using a log-rank test. A *p* value < 0.05 will be considered statistically significant.

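### Unadjusted Pearson correlations are the stated test of the mechanistic secondary endpoint; in a mixed population they can partly reflect case mix, and an adjusted analysis should carry the mechanistic statements

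*Protocol article*

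**What the plan says.** All references are to the protocol article.

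- **Purpose.** Study objectives and hypotheses introduces the plaque–laboratory relationships with "In order to identify the mechanisms of plaque stability and regression". It speaks of studying them in the two treatment groups, which points to analysis by arm.
- **Endpoint.** Study endpoints lists, as the fifth secondary endpoint, "relationships between the changes in tissue components of plaque and changes in laboratory findings".
- **Method.** Statistical analyses gives "Pearson correlation test will be used to evaluate the correlation between the changes in percentage NCV and absolute NCV, and changes in laboratory findings". For the other IVUS and angiographic parameters it adds: "Correlations between these parameters and laboratory variables will be evaluated by the Pearson correlation test". The threshold is p < 0.05. Neither sentence names a covariate or stratum.
- **Adjusted analysis.** The same section plans a multivariable linear regression for independent predictors of the reduction in percentage NCV. It does not say that laboratory change or presentation enters that model, and it names no such model for absolute NCV or the other parameters.
- **Baseline blood.** Study design and subjects: "Biochemical laboratory tests (fasting state) will be performed at the time of CAG". Laboratory assessment includes hs-CRP and lipids.
- **Case mix.** Randomisation is stratified by "age, sex, and clinical presentation (acute coronary syndrome or not", so both presentations are enrolled. Study population and entry criteria requires "baseline LDLc ≥ 70 mg/dL and non-HDLc ≥ 130 mg/dL in statin-naïve patients"; patients already on a statin need LDLc of at most 100 and non-HDLc of at least 100 mg/dL. Prior statin use is not a randomisation stratum.

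**The concern.** A correlation across patients is an observational association, even inside a randomised trial. Randomisation balances the arms; it does not balance patients with a large laboratory change against patients with a small one.

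Two features could shift laboratory change whatever the added drug does. Some baseline samples are taken during an acute presentation, which may matter for an inflammatory marker such as hs-CRP. And statin-naive patients start rosuvastatin in the trial, while others were already on a statin. If plaque change also differs by either feature, the raw correlation absorbs that difference. Running the correlations within each arm does not remove it, because each arm contains both kinds of patient.

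At stake is how the mechanistic endpoint is read: a correlation produced by who was enrolled could be reported as a mechanism of plaque regression.

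**Working it through.** **The plan's own figures.** Sample size calculations gives a difference of 4.78, SD 7.82, 80% power and two-sided alpha 0.05:

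n per arm = 2 × (1.960 + 0.842)² × 7.82² / 4.78² ≈ 42.0

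This agrees with the stated 42 (power at 42 is 79.99% by the normal formula). Then 42 / 0.80 = 52.5, rounded up to 53 per arm, 106 in total. The evaluable numbers are therefore 42 per arm and 84 pooled. The article gives no power for the correlations and needs none.

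**Assumptions, not in the documents.** One binary stratum (ACS or not, or statin-naive or not) with share p. Its two levels differ by d₁ within-stratum SDs in laboratory change and d₂ in NCV change. There is no correlation within strata.

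**Induced correlation.**

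r = p(1−p)d₁d₂ / √{[1 + p(1−p)d₁²][1 + p(1−p)d₂²]}

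Example with p = 0.5, d₁ = 1.0, d₂ = 0.5: r = 0.125 / √(1.25 × 1.0625) = 0.108.

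**False-positive rate** (Fisher z), with ζ = atanh(r) × √(n − 3):

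rate = 1 − Φ(1.96 − ζ) + Φ(−1.96 − ζ)

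Same example at n = 84: ζ = 0.109 × 9 = 0.98, rate = 16.5%.

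Results for p = 0.5:

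| NCV gap (SD) | Laboratory gap (SD) | Induced r | n = 42 (one arm) | n = 84 (pooled) |
|---|---|---|---|---|
| 0.25 | 1.0 | 0.055 | 6.4% | 7.9% |
| 0.25 | 1.5 | 0.074 | 7.5% | 10.3% |
| 0.25 | 2.0 | 0.088 | 8.5% | 12.4% |
| 0.5 | 1.0 | 0.108 | 10.4% | 16.5% |
| 0.5 | 1.5 | 0.146 | 15.0% | 26.1% |
| 0.5 | 2.0 | 0.171 | 19.1% | 34.4% |

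Simulation (40,000 runs per cell) agrees within half a percentage point. The partial correlation given the stratum rejects in 4.8–5.2% of runs in every cell.

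**Sensitivity.**
- At a 30% share, the n = 42 rates become 6.0–7.7% (0.25 SD) and 9.0–15.8% (0.5 SD). At n = 84 they are 7.1–10.7% and 13.4–27.8%.
- With an NCV gap of 0.1 SD, every rate is between 5% and just over 6%.
- If only one of the two changes differs by stratum, the induced r is 0 and there is no inflation.

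**Scale of the assumed NCV gap.** The planned drug effect is 4.78 / 7.82 = 0.61 SD. A gap of 0.5 SD is 0.5 / 0.61 = 0.82 of that effect, and 0.25 SD is 0.41 of it.

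**The case against.** The strongest objections are these.

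1. **An adjusted analysis is already planned.** The multivariable regression targets percentage NCV, the sample-size endpoint, and its covariate list is ordinary material for an analysis plan not shown here. This stands in part. A reader might infer that the plan has no adjusted analysis at all, and that would be wrong. But the model is described for percentage NCV only, while the article names Pearson correlation as the method for absolute NCV and the other parameters.
2. **The size is assumed.** This stands. No document gives stratum shares or gaps, and with an NCV gap of 0.25 SD the inflation is small. In every row of the table the induced r is below the significance limit (|r| = 0.304 at n = 42, 0.215 at n = 84), so case mix raises the chance of a false positive without making one likely.
3. **The pooled rates are not the natural headline.** The objectives section points to analysis by arm, so the n = 42 column is the better guide.
4. **Adjustment can remove the mechanism.** If statin-naive patients have a larger LDLc fall and that fall reduces necrotic core, adjusting for prior statin discards real exposure variation. This stands for lipids, and it is why prior statin belongs in a sensitivity analysis. The same argument against adjusting for arm is weaker. The between-arm contrast is shared by every marker that fenofibrate changes, so it cannot single one out, and the arms are compared directly elsewhere.
5. **The language is cautious.** The Discussion and Conclusions speak of plausible mechanisms, and nothing commits the sponsor to a causal reading. That lowers the stakes; it does not make the raw correlation the better basis.

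**Conclusion.** The point holds as a weakness of method in a secondary endpoint. The article fixes an unadjusted test for a stated mechanistic purpose in a population mixed on two features that could affect laboratory change, and randomisation does not protect that test.

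The size is conditional: about 6–9% by arm with a 0.25 SD gap in NCV change and 10–19% with 0.5 SD, or 8–12% and 17–34% if the arms are pooled, against a nominal 5%. These figures assume a 50% share, a laboratory gap of 1.0–2.0 SD and no within-stratum correlation. Both changes must differ by stratum for any inflation to arise.

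A reader might go further and conclude that a significant correlation in this trial would be an artefact, or that the treatment comparison is compromised. The documents support neither. They contain no evidence on how plaque change varies by presentation or prior statin, and the randomised primary comparison does not use these correlations.

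**What to change.** Keep the Pearson correlations, label them exploratory, and add the following:

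- Base mechanistic statements on partial correlations, or on linear regression of plaque change on laboratory change, adjusted for ACS versus non-ACS and, where the arms are pooled, for treatment arm. Apply this to absolute NCV and the other IVUS parameters as well as to percentage NCV.
- Show the hs-CRP estimates separately in ACS and non-ACS patients.
- Add prior statin use as a sensitivity adjustment, noting that for LDLc it may remove genuine exposure variation.

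The cost is two or three degrees of freedom and slightly more analysis work. No new data are needed: presentation is a randomisation stratum, and prior statin use decides which lipid limits apply at entry. Adjusted estimates will be less precise where a stratum explains much of the laboratory change.

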## Statistical considerations

### Sample size calculations

Based on a previous study [15], a sample size of approximately 42 patients per treatment group was calculated to provide 80% power (assuming a standard deviation of 7.82) to detect a difference of 4.78 in percentage NCV and to detect the superiority of statin plus fenofibrate compared to statin alone with a two-sided alpha level of 0.05. With a statin plus fenofibrate:satin alone sampling ratio of 1:1 and a dropout rate of 20%, a final sample size of 53 patients per treatment group (total 106 patients) was specified in order to provide an adequate number of evaluable patients. To the best of the researchers’ knowledge, no study has been conducted on the change of tissue characteristics after fenofibrate treatment. We hypothesized that fenofibrate has an effect on percentage NCV as much as that of 10 mg atorvastatin [15]. In addition, a previous study [16] consisting of 100 patients with non-significant lesions demonstrated a significant decrease in NCV in the rosuvastatin (10 mg/day) treated group but not in the simvastatin treated group (20 mg/day).

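### Change in TCFA is compared by a chi-square or Fisher test that does not condition on baseline TCFA: valid overall, but usually less efficient and unprotected against a large chance imbalance

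*Protocol article*

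**What the plan says.** Study endpoints lists "change in plaque phenotypes such as TCFA" as the second secondary endpoint. Study objectives and hypotheses names "the incidence of and changes in thin cap fibroatheroma (TCFA"), so it covers both incidence and change. Statistical analyses fixes the test: "Changes in the phenotypes of the index lesions between the two groups will be compared by" chi-square or Fisher's exact test, and a p "value < 0.05 will be considered statistically significant".

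Three other places bear on this:

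- **VH-IVUS and quantitative coronary angiography:** presence of TCFA is among the variables measured at baseline and after 12 months.
- **Randomization, interventions, and data assessment:** randomisation is stratified by age, sex and clinical presentation, not by baseline TCFA.
- **Statistical analyses:** the only multivariable model is for predictors of the reduction in percentage necrotic core volume (NCV). No adjusted analysis of TCFA is named.

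The article does not say how change in TCFA is coded, and it gives no TCFA rate or TCFA power.

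**The concern.** Only a lesion with TCFA at baseline can lose it, and only a lesion without TCFA can gain it. A single table over all lesions, by arm, mixes these two risk sets. Three codings fit such a table: presence at 12 months, resolved yes/no, and resolved/unchanged/new. The first leaves out the baseline reading. The other two use it to define change but do not condition on it, so the count of changes in an arm depends partly on how many of its lesions were able to change.

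Two things are at stake. The comparison may have less power than the same data allow. And if the arms differ markedly in baseline TCFA by chance, part of that difference carries into the result. TCFA matters to the trial's argument: the Discussion section on the choice of VH-IVUS cites it as an independent predictor of cardiovascular events and names its change as one reason for using the technique.

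**Working it through.** **1. The plan's own sample size.** The inputs are from Sample size calculations: "to provide 80% power (assuming a standard deviation of 7.82"), "to detect a difference of 4.78 in percentage NCV", and "with a two-sided alpha level of 0.05".

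n per arm = 2 × (1.960 + 0.842)² × (7.82/4.78)² = 2 × 7.849 × 2.676 ≈ 42.0

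The article says "a sample size of approximately 42 patients per treatment group was calculated". Strict rounding up, or the t-based formula, gives 43, and z-based power at 42 is 79.99%. With 20% dropout, 42/0.80 = 52.5, so 53 per arm. The design figure reproduces. It concerns percentage NCV; nothing is powered on TCFA. I use 42 evaluable per arm below.

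**2. Why the baseline mix matters.** Assume no drug effect, loss of TCFA 30% and new TCFA 12% in both arms, and baseline TCFA of 50% v 30%. The expected results are:

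- TCFA at 12 months: 0.50 × 0.70 + 0.50 × 0.12 = 41.0%, v 0.30 × 0.70 + 0.70 × 0.12 = 29.4%
- resolved, among all lesions: 0.50 × 0.30 = 15%, v 0.30 × 0.30 = 9%

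The arm with more TCFA at baseline looks worse on the first coding and better on the second. Within each baseline stratum there is no difference.

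**3. The comparator.** The Cochran-Mantel-Haenszel (CMH) statistic is [Σ(aₖ − Eₖ)]² / ΣVₖ over the strata baseline TCFA yes and no. Here aₖ is the number with TCFA at 12 months in one arm, Eₖ = n₁ₖm₁ₖ/Nₖ, and Vₖ = n₁ₖn₀ₖm₁ₖm₀ₖ/[Nₖ²(Nₖ − 1)].

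**4. Power (simulation, two-sided 0.05, all TCFA rates assumed).** The first scenario has 40% TCFA at baseline, loss 30% v 60%, and new TCFA 12% v 5%:

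| Test | Power |
|---|---|
| Chi-square, resolved/unchanged/new | 27% |
| Chi-square, resolved yes/no | 31% |
| Fisher, 12-month status | 31% |
| Chi-square, 12-month status | 39% |
| Exact CMH | 43% |
| Asymptotic CMH | 50% |

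Twelve further scenarios used baseline TCFA 30–60%, control persistence 50–95%, treated persistence 20 to 40 points lower, and new TCFA 2–10%. Power relative to asymptotic CMH was:

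- chi-square on 12-month status: 0.46 to 0.95, median about 0.76, typically about 11 percentage points lower
- Fisher on 12-month status: 0.32 to 0.76, partly through Fisher's own conservatism
- chi-square on resolved yes/no: 0.55 to 1.13
- chi-square on resolved/unchanged/new: 0.45 to 0.91

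For example, with baseline 50%, persistence 70% v 40% and new TCFA 5%, 12-month chi-square has 33% and CMH 44%. With persistence 90% v 60% and new TCFA 2%, the figures are 29% and 58%.

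**5. Type I error over all randomisations.** 12-month chi-square 4.5–6.0%, Fisher 2.7–3.7%, CMH 4.6–5.2%.

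**6. Type I error given an imbalance.** At 40% prevalence the standard deviation of the baseline difference is √(2 × 0.40 × 0.60/42) = 0.107. A gap of 20 points is 0.20/0.107 = 1.87 standard deviations, so about 6% of trials have a gap that large or larger. Simulation also gives 6%, and 31–32% for a gap of 10 points or more.

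- **Gap fixed near 20 points, moderate loss rates:** the unstratified chi-square codings reject a true null 7–14% of the time, CMH about 5%.
- **Gap fixed near 10 points** (19 v 15 patients; 4/42 = 9.5 points): 4–5%, so no inflation.
- **Sensitivity:** among null trials with a gap of 8 patients or more (7–10% of trials, including larger gaps), 12-month chi-square rejected in 15–42% and CMH in 3–5%. The 42% arises with 90% persistence in both arms. In that same case resolved yes/no rejected in 5% and the three-category test in 3%, so the distortion depends on the coding.

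**The case against.** The strongest reply is that the named test is valid and the rest is preference. Much of this stands.

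- **Baseline is not ignored.** A reader might infer that the plan discards it. The endpoint is worded as a change, which needs both readings. The accurate statement is that the test does not condition on baseline.
- **The coding is open.** A test of loss confined to lesions with TCFA at baseline would also fit the sentence, and pooling would not affect it. A condensed article may leave coding to the full protocol or SAP, so its absence is not the point here. The test itself is stated, without stratification.
- **Stratifying does not always win.** In the first scenario, fully exact CMH has 43%, not the 50% of the asymptotic test. When the drug does not affect new TCFA (5% v 5%), exact CMH has 28%, below 31% for resolved yes/no and 42% for a chi-square confined to lesions with TCFA at baseline.
- **The endpoint is secondary and unpowered.** The Conclusions tie reduction and stabilisation to NCV, the primary endpoint.

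What remains is that the protocol names a test for this endpoint, that the baseline reading will be in hand, and that nothing in the randomisation balances it.

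**Conclusion.** The point holds as a modest improvement to a secondary analysis. The unstratified test usually has less power: typically about a quarter less for 12-month status, with a range from near zero (or a slight gain for resolved yes/no) to about half. These sizes rest on 42 evaluable patients per arm and on TCFA rates that the documents do not give.

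Two stronger readings are tempting and are not supported. One is that the test costs half the power. For 12-month chi-square, that appears only when control-arm persistence is about 90% or more and new TCFA is rare; otherwise it takes Fisher's test or the three-category coding under some rates. The other is that the test produces false drug effects in general. Overall type I error is about 5% or lower. Inflation is confined to the roughly 6% of trials with a baseline gap of about 20 points, where it is about 7–14% at moderate loss rates, against about 5% for the stratified test. A gap of about 10 points causes none.

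**What to change.** For TCFA, replace the sentence in Statistical analyses with wording such as:

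*Presence of TCFA at 12 months will be compared between arms by a Cochran-Mantel-Haenszel test stratified by baseline TCFA (asymptotic, or mid-p when counts are sparse), or by logistic regression with baseline TCFA as covariate, and reported as an odds ratio with 95% CI. Loss of TCFA will be reported among lesions with TCFA at baseline, and new TCFA among lesions without it.*

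One of the two methods should be named as the main one before the data are seen. A fully exact CMH test is not advised as the default, because it gives back much of the gain (43% against 50% in the first scenario).

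The cost is one changed sentence. No new data are needed, since both readings are already planned. The downside is slightly less power than a resolution-only test if the drug affects only the loss of TCFA.

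### Randomisation is stratified by clinical presentation but the MACE log-rank test is not; stratifying by ACS status would be a small improvement to a valid secondary analysis

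*Protocol article*

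**What the plan says.** Under Randomization, interventions, and data assessment, the protocol article describes a table based on "stratified randomization according to subjects’ age, sex, and clinical presentation (acute coronary syndrome or not"). Study design and subjects names the same three factors in other words, a table "made by matches of age, sex, presentation of coronary artery disease and sequentially numbered".

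MACE is a secondary endpoint. Study objectives and hypotheses says that "secondary endpoints will include comparisons of major adverse cardiac events (MACEs) at 12 months". Under Statistical analyses the test is given as: "The composite endpoint of CV events will be analyzed by comparing the Kaplan–Meier event rates using a log-rank test". No strata or covariates are named for it. The threshold is general: "A *p* value < 0.05 will be considered statistically significant".

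The only power statement concerns percentage necrotic core volume (NCV). The sample size "was calculated to provide 80% power (assuming a standard deviation of 7.82") for a difference of 4.78, "with a two-sided alpha level of 0.05". No event count, hazard ratio or power is given for MACE.

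**The concern.** Stratified allocation forces the arms to be nearly balanced on the stratifying factors. If one of them predicts the outcome, the true variance of the between-arm comparison is smaller than a plain log-rank test assumes. The test then rejects less often than its nominal 5% under no effect, and it loses some power. A log-rank test stratified by the same factor compares patients within strata and removes the mismatch.

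Presentation is the factor most worth considering, since ACS and non-ACS patients may well differ in 12-month event risk. MACE is the trial's only clinical-event efficacy endpoint, and the abstract says the trial will address CV events. It is reasonable to want the stated test to use a factor that the design already uses.

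**Working it through.** **1. The plan's own figure.** For percentage NCV, n per arm = 2(1.960 + 0.842)² × (7.82/4.78)² = 2 × 7.849 × 2.676 = 42.0. The plan says approximately 42. With 20% dropout, 42/0.8 = 52.5, rounded up to 53 per arm and 106 in total. The figure reproduces, but it says nothing about MACE.

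**2. What MACE would need.** For 80% power at a hazard ratio (HR) of 0.5, two-sided 5%:
- Schoenfeld: 4 × 7.849/(ln 0.5)² = 31.40/0.4805 = 65.3, so 66 events.
- Freedman: 7.849 × (1.5/0.5)² = 70.6, so 71 events.

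At assumed 12-month control rates of 5% to 20%, 106 patients give about 5 to 21 events under no effect and about 4 to 16 under HR 0.5.

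**3. The two tests.** Over event times, U = Σ(g − p) and V = Σp(1 − p), where g marks the treated arm and p is the treated share of those still at risk. The plain test uses Z = U/√V over all patients. The stratified test computes U and V within each stratum and uses Z = ΣU/√ΣV.

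**4. Simulation with blocked allocation.** Assumed, because the documents do not give them: 50% ACS, permuted blocks of 4 in 8 strata (one age cut × sex × ACS), exponential event times, censoring at 12 months, HR 0.5 for power. There were 10,000 trials per run. Ranges are over repeat runs. The implied ACS hazard ratio is ln(1 − ACS rate)/ln(1 − non-ACS rate); for 25%/5% that is 0.2877/0.0513 = 5.6.

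| Control rate, ACS/non-ACS | Implied ACS HR | Type I error, plain v stratified | Power, plain v stratified | Change (points) |
|---|---|---|---|---|
| 35%/5% | 8.4 | 3.2–3.5% v 4.6–5.1% | 23.0–23.6% v 27.1–27.5% | +3.7 to +4.1 |
| 25%/5% | 5.6 | 4.1–4.2% v 4.9–5.0% | 19.7–20.1% v 21.2–21.9% | +1.5 to +2.0 |
| 15%/5% | 3.2 | 4.4–4.8% v 4.7–5.1% | 14.2–14.7% v 14.8–15.0% | +0.3 to +0.6 |
| 8%/3% | 2.7 | 4.5% v 4.5–4.7% | 8.5–8.7% v 8.5–8.9% | 0.0 to +0.2 |
| 10%/10% | 1 | 5.0% v 5.0% | 15.3–15.5% v 15.2–15.6% | −0.1 to +0.1 |
| 5%/5% | 1 | not tabulated | 7.7% v 7.6% | −0.1 |

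**5. Separate check by overall rate.** Arms balanced within ACS stratum, 50% ACS, 40,000 trials per case. Power at HR 0.5, plain v stratified:

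| Overall control rate | ACS HR 1 | ACS HR 2 | ACS HR 4 |
|---|---|---|---|
| 5% | 8.3% v 8.2% | 8.1% v 8.1% | 8.3% v 8.7% |
| 10% | 15.6% v 15.1% | 14.9% v 14.9% | 14.5% v 15.6% |
| 20% | 26.8% v 26.8% | 26.8% v 27.3% | 25.3% v 27.5% |

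The change runs from about −0.5 to +2.2 points. Type I error is 4.1–5.1% for the plain test and 4.4–5.0% for the stratified test.

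**6. All three factors.** With eight cells of assumed size (24, 24, 8, 8, 16, 16, 5 and 5 patients) and ACS HR 1 or 2, full stratification changes power by −0.7 to +0.4 points against the plain test. The losses are largest at a 5% event rate (8.3% falls to 7.6–7.9%).

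**7. Where the mechanism would matter.** At a 70% event rate (about 74 events) and ACS HR 4, the plain test's type I error falls to 2.4% and its power is 64% against 78% stratified. This trial is far from that setting.

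**The case against.** The strongest reply is that nothing here is wrong. The plain log-rank test does not inflate false positives and contradicts no other section. A condensed article may leave the strata of a secondary test to a statistical analysis plan that is not shown. MACE is unpowered under either test, and the article already lists small size and short follow-up as limitations. The gains above 1 point need an ACS hazard ratio of about 4 or more together with enough events, and the documents supply neither.

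Most of this stands, and it limits the point to a minor one. It does not remove it: the article names a specific test for MACE and a specific stratified randomisation, and the two can be aligned at almost no cost.

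Three stronger readings are tempting, and the documents do not support them:
- *A reader might infer that the planned test is conservative and wastes power as a matter of fact.* That holds only if ACS is prognostic and events are sufficient. At 8%/3% the two tests are practically the same.
- *A reader might infer that stratifying is free.* With ACS not prognostic, one case lost about 0.5 points, although the blocked runs showed about 0.
- *A reader might infer that chance imbalance from incomplete blocks biases the plain test.* The blocked simulation includes incomplete blocks, and the plain test's error stayed at or below 5%.

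**Conclusion.** The point holds as a minor improvement. The MACE test as stated does not use the factors by which patients are randomised. It remains valid and would be mildly conservative if presentation predicts MACE. Stratifying by ACS is worth about 0 points of power at 4 to 8 events or when ACS is not prognostic (as low as −0.5), about +2 at 25%/5% and about +4 at 35%/5%. All of these figures rest on assumed event rates, an assumed 50% ACS share and HR 0.5. Power is roughly 8–28% with either test. The missing strata are therefore not the reason the MACE comparison is weak; the small number of events is. The primary NCV comparison is not affected by this point.

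**What to change.** Under Statistical analyses, reword the MACE sentence along these lines: *the MACE composite will be compared by a log-rank test stratified by clinical presentation (ACS or not); the unstratified log-rank test will be reported as a sensitivity analysis.*

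Use presentation only. Stratifying by all three factors gives thin cells with few events and can lose power.

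The cost is one sentence and no new data. The downside is a negligible loss of power if ACS turns out not to be prognostic. The article reports 102 of 106 patients recruited with completion still ahead, so at that stage the choice could still be fixed before the data were analysed. Fixing it then also prevents a choice between two tests after the results are known.
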